**Email: [[contact]](mailto:[contact])**

In case of malfunction or any other issue preventing emailing (and only in this case), the form can be faxed to the sponsor at [name].

The investigator will note in particular for each event:

- Its description as clearly as possible according to the medical terminology,
- The intensity,
- The start and end date of the event,
- The measures taken and whether or not corrective treatment is necessary,
- Its clinical course. In case of a non-fatal event, progression should be followed until recovery or return to the previous state or stabilization of any sequelae,

- Its cause, and in particular the causal relationship between this event and the study or a research-related constraint (additional examinations requested as part of the research, etc.).

The investigator should also attach to the serious adverse event report, whenever possible:

- A copy of the hospitalization or prolongation of hospitalization report,
- A copy of all the results of additional tests performed, including relevant negative results with normal laboratory values,
- Any other document he/she deems useful and relevant.

All these documents must be anonymized.

Additional information may be requested (by fax, phone, email, or visit) by the sponsor.

#### *8-7-5-7 SAE follow-up*

The investigator is responsible for appropriate medical follow-up of the patients until resolution or stabilization of the event or death of the patient. This may sometimes mean that this follow-up will continue after the patient has withdrawn from the trial.

He/she forwards the additional information to the Sponsor using an SAE notification form (by checking the Follow-up No. X box to clarify that this is a follow-up and not an initial report). He/she also forwards the last follow-up upon resolution or stabilization of the SAE.

He/she keeps the documents regarding the presumed SAE in order to allow, if necessary, the previously sent information to be completed.

He/she responds to requests for additional information from the Sponsor to document the initial observation.

#### *8-7-2-8 Sponsor responsibilities*

##### ➤ Recording of pharmacovigilance data and immediate reporting of unexpected SAEs

The sponsor will be responsible for maintaining and storing all study-related vigilance data.

The sponsor will also be responsible for reporting all suspected unexpected serious adverse reactions (SUSAR) to the ANSM, the relevant EC and for informing the investigators in accordance with applicable regulations.

##### ➤ New facts

As with all research involving human subjects, the sponsor will send to the investigators concerned any information likely to affect the safety of subjects (Art. R1123-52 CSP (*Code de la santé publique* [French Public Health Code])) and will immediately inform the competent authority and the ethics committee of new facts and, if applicable, the measures taken (Art. R1123-59 of the CSP).

##### ➤ Periodic safety reports

---

 **New fact:** any new data that could lead to a reassessment of the risk-benefit ratio or the research product of the research, changes in the use of this product, in the conduct of the research, or documents relating to the research, or could suspend or interrupt or modify the research protocol or similar research studies (CSP, Art. R1123-46, 12°).

The sponsor is responsible for preparing and drafting periodic safety reports and submitting them to the ANSM and relevant EC in accordance with applicable regulations.

#### **8-7-6 Benign histological abnormalities**

- Number and type of benign histologic abnormalities in the tube or adjoining ovary specimen

#### **8-7-7 Satisfaction questionnaire**

A questionnaire will be given to the patients who have had surgery, to give them a voice about their feelings and their satisfaction. This questionnaire consists of 5 items to assess:

- patient concerns about their decision to opt for a fimbriectomy – and, if applicable, oophorectomy before menopause age;
- the respective symptoms associated with these interventions,
- and if patients would be willing to recommend fimbriectomy if this technique was clinically validated.

### **8-8 Statistical methodology**

#### **8-8-1 Determination of the number of patients and study discontinuation criteria**

The cumulative incidence of pelvic tumors is estimated to be around 10% at 10 years in BRCA mutated women in the absence of prophylactic surgery (Chen et al Meta-analysis of BRCA1 and BRCA2 penetrance JCO 2007; 25:1329-33), corresponding to an “acceptable” rate of 3% at 3 years. A dynamic method for interim analyses for rare events will be used to discontinue the study if, within 3 years, the number of pelvic tumors reaches 2 for 12 participants, 3 for 27 participants, 4 for 46 participants, and 5 for 66 participants for a maximum number of patients of 120 (Kramar A, Bascoul-Mollevi C. Early Stopping Rules in Clinical Trials Based on Sequential Monitoring of Serious Events. Med Decis making 2009;29:343-350). These decision rules correspond to the comparison of the lower limit of the confidence intervals adjusted on the information fraction and on a concave alpha spending function. Three years after the last patient is enrolled, if 8 pelvic tumors are observed among the 120 patients, the treatment strategy will be considered insufficiently promising as the lower limit of the one sided 90% confidence interval will not contain the acceptable value of 3%.

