| METHODOLOGY/NUMBER OF PATIENTS | 
The cumulative incidence of pelvic tumors is estimated to be around 10% at 10 years in BRCA mutated women in the absence of prophylactic surgery (Chen et al Meta-analysis of BRCA1 and BRCA2 penetrance JCO 2007; 25:1329-33), corresponding to an "acceptable" rate of 3% at 3 years. A dynamic method for interim analyses for rare events will be used to discontinue the study if, within 3 years, the number of pelvic tumors reaches 2 for 12 participants, 3 for 27 participants, 4 for 46 participants, and 5 for 66 participants for a maximum number of patients of 120* (Kramar A, Bascoul-Mollevi C. Early Stopping Rules in Clinical Trials Based on Sequential Monitoring of Serious Adverse Events. Med Decis making 2009; 29: 343-350). These decision rules correspond to the comparison of the lower limit of the confidence intervals adjusted on the information fraction and on a concave alpha spending function.
 
Three years after the last patient is enrolled, if 8 pelvic tumors are observed among the 120 patients, the treatment strategy will be considered insufficiently promising as the lower limit of the one sided 90% confidence interval will not contain the acceptable value of 3%.
 
*In the end, 123 patients were enrolled in this research; indeed, 3 patients were added to replace patients who had agreed to participate in the study but could not be assessed for the preventive benefit of fimbriectomy (example: non-operated patients)
                                                                                                                                                                                                                                                                                                                                                                                                                                                                                                                                                                                                                                                                      |                     |         |                          |                     |               |                     |

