### **8-6-3 Follow-up report**

The primary objective of radical fimbriectomy is to reduce the risk of serous pelvic carcinoma (ovarian or peritoneal) with a predominant tubal origin, while awaiting definitive castration.

Since a large portion of the ovaries is left in place, there is a residual risk of high-grade serous carcinoma that is probably very low but not zero. It could be due to the degeneration of STIC tissue left in place on the ovary (but which would also exist on the fimbriectomy specimen) or by the degeneration of inclusion cysts [Kurman, 2010]. Finally, the development of any other type 1 tumor can be observed from tissue included in these same cysts or a non-epithelial tumor, germ cell tumor, or sex cords that is not related to the BRCA gene abnormality.

Any abnormal abdominal or gynecological symptoms, whether there is a genetic background or not, should result in appropriate imaging being performed, possibly repeated or supplemented by surgery. The follow-up of these asymptomatic women at risk should also be considered.

Surveillance methods have proved ineffective at screening for high-grade serous carcinoma. However, they make more sense when it comes to detecting a type 1 tumor or a non-epithelial tumor that usually grows more slowly.

To date, the screening combining the annual CA-125 blood test followed-up according to its transvaginal ultrasound result, appears to be the combination that leads to the least "unnecessary" surgeries while detecting most early cancers, as shown in the largest randomized screening study conducted to date [Menon 2009].

For other women without lesions identified on the fimbriectomy specimens, we thus propose to base the pelvic monitoring procedures of these women on this protocol. This gynecological screening will be combined with breast disease screening.

If a test is abnormal, it is repeated. In case of persistent abnormality, further clinical assessment (MRI) or surgical follow-up will be discussed.

| Type of Assessment                                                                                               | Timeline - Comments                                                |
|------------------------------------------------------------------------------------------------------------------|--------------------------------------------------------------------|

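### The 3% benchmark at 3 years is the protocol's own no-surgery risk, so the decision rule screens for excess risk and a pass says almost nothing about risk reduction

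*Protocol*

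**What the plan says.** Section 8-8-1 of the protocol, repeated in the synopsis, gives a single rate. It takes the cumulative incidence of pelvic tumors as "around 10% at 10 years in BRCA mutated women in the absence of prophylactic surgery" and describes this figure as "corresponding to an “acceptable” rate of 3% at 3 years". Early stopping concerns events in the first 3 years and is triggered when "the number of pelvic tumors reaches 2 for 12 participants, 3 for 27 participants, 4 for 46 participants, and 5 for 66 participants". The planned ceiling on enrolment is 120 women. The last step comes three years after the last enrolment: "if 8 pelvic tumors are observed among the 120 patients, the treatment strategy will be considered insufficiently promising", because the one-sided 90% lower limit would then exclude 3%.

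The section gives no target rate below 3%, no criterion on an upper limit and no power.

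Section 8-6-3 states the purpose of the operation: "The primary objective of radical fimbriectomy is to reduce the risk of serous pelvic carcinoma". Section 7-1 states the trial's primary objective differently, as assessing incidence, and section 8-8-2 plans to estimate cumulative incidence with competing risks.

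**The concern.** The rate described as acceptable after surgery is the rate the protocol expects without surgery. A rule that fails the strategy only when the lower limit exceeds that rate asks whether women fare worse than if nothing had been done. The operation is offered to lower risk, and the rule does not test that.

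The wording adds to the problem. Only failure is defined, as "the treatment strategy will be considered insufficiently promising", so a result below 8 tumors invites the opposite conclusion, that the strategy is promising. The eligible women are those to whom adnexectomy is offered first (section 8-2). A pass taken as evidence of protection would carry weight in the decision to delay that surgery, although a procedure with no effect would usually obtain the same result.

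**Working it through.** **Inputs, all from section 8-8-1:** 10% at 10 years without surgery; 3% at 3 years; boundaries 2/12, 3/27, 4/46 and 5/66; final rule of 8 or more among 120. Assumption: every woman has a known 3-year outcome, and outcomes are independent.

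**1. Origin of the 3%.** Linear: 10% × 3/10 = 3.0%. Constant hazard: 1 − (1 − 0.10)^(3/10) = 3.11%. The benchmark is the untreated risk rescaled to 3 years.

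**2. The plan's own figure.** The exact (Clopper-Pearson) one-sided 90% lower limit for 8/120 is 3.92%, which is above 3%, so the statement about 8 tumors is true. The interim sizes 12, 27, 46 and 66 are the largest n at which 2, 3, 4 and 5 events give an exact one-sided 95% lower limit above 3%. Every boundary is therefore a test for a rate above 3%.

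**3. Chance of passing.** The final count alone is P(X ≤ 7) with X ~ Binomial(120, p). The whole rule is an exact binomial recursion that removes paths reaching an interim boundary and then applies the final count.

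| True 3-year risk | Meaning against 3% | Pass, final count only | Pass, whole rule |
|---|---|---|---|
| 1.5% | halved | >99.9% | 97.9% |
| 2% | reduced by a third | 99.7% | 95.7% |
| 3% | no effect | 97.1% | 88.0% |
| 6% | doubled | 56.8% | 42.6% |

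At 3% the whole-rule failure probability is 0.110 (stopped early) + 0.010 (failed at the end) = 0.120. At 3.11% the pass probabilities are 96.6% and 86.8%.

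The gap between no effect and a halved risk is 97.9 − 88.0 = about 10 percentage points. For an 80% chance of failing the whole rule, the true 3-year risk must be about 7.75%, or 7.75/3 = about 2.6 times the untreated rate.

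**4. What 120 women could show at 3 years.** The exact one-sided 95% upper limit with 0 events is 1 − 0.05^(1/120) = 2.47%. With 1 event it is 3.89%. Only 0/120 puts the limit below 3%. If the operation truly halved the risk, the chance of 0 events is 0.985^120 = 16%. Moving to an upper-limit criterion at 3 years would therefore be correctly framed but would seldom be met.

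**5. Sensitivity to the benchmark.** If untreated risk is lower than 10% at 10 years, a procedure with no effect passes more often than 88%. The protocol gives reasons to expect this: section 6 quotes 5–10% for BRCA1 and 1–5% for BRCA2 before age 50, and section 8-2 admits women on family history alone. In the other direction, an assumed 15% at 10 years is 1 − 0.85^0.3 = 4.8% at 3 years, and 63% would still pass.

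**The case against.** The strongest reply is that this is a phase II study whose stated objective is to assess incidence (section 7-1), described as a feasibility study in section 8-1. No hypothesis of superiority over no surgery is written anywhere. The heading of 8-8-1 refers to discontinuation criteria, and the cited method is sequential monitoring of serious events, where a one-sided rule against excess is normal. The protocol never says that fewer than 8 tumors means efficacy.

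Much of this stands. A reader might infer that the trial cannot answer its own question. The documents do not support that: the incidence will be estimated whatever the rule says. The interim boundaries are also defensible as harm monitoring. The reply does not cover the final step, which passes judgment on the treatment strategy against a rate labelled acceptable without saying that it is the untreated rate.

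Three further inferences go too far:

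- That the rule can condemn only a harmful procedure. By chance it also fails one with no effect 12% of the time, and one with a true risk of 2% about 4% of the time.
- That it cannot separate protection from none at all. Separation is weak (88% against 98% for a halved risk), but not absent.
- That a doubled risk would usually pass. The 57% refers to the final count alone; with the interim boundaries it is 43%, so a doubled risk more often fails.

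A tempting remedy also fails: declaring success at 10 years if at most 6 of 120 women have a tumor. Nominally, P(X ≤ 6) at 10% is 3.8%. But oophorectomy is a competing event (section 8-7-1), and participation ends at oophorectomy or menopause (section 8-5). Assume constant hazards and that oophorectomy alone would reach 50% by 10 years. A procedure with no effect would then show an incidence of 7.3% and meet the criterion 22% of the time; at 70% oophorectomy, 44% of the time.

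**Conclusion.** The concern holds for the decision rule. The acceptable 3% is the protocol's no-surgery risk, and a pass gives almost no evidence of risk reduction: 88% of trials of a procedure with no effect would pass the whole rule (97% on the final count), against 98% if the risk were halved. These figures assume complete 3-year outcomes and an untreated 3-year risk of 3%; step 5 shows how they move with that risk. The planned incidence estimates are not affected, and the monitoring boundaries may stay as harm or futility rules if they are labelled so.

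One separate inconsistency should be reconciled at the same time. At the stated one-sided 90% level, 7/120 already excludes 3% (exact lower limit 3.27%). A cutoff of 8 fits a one-sided 95% limit instead (7/120 gives 2.77%, 8/120 gives 3.36%). The conclusion here does not depend on it.

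**What to change.** In section 8-8-1 and the synopsis:

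1. State that 3% at 3 years is the untreated rate, and that the interim boundaries and the 8/120 rule are harm or futility monitoring.
2. State that fewer than 8 tumors means only that the incidence was not shown to exceed the no-surgery rate, and that it supports no efficacy claim.
3. Report the one-sided 95% upper limit of the 3-year incidence beside the 3% benchmark, noting that with 120 women only 0 events brings it below 3% (2.5%; 1 event gives 3.9%).
4. Label any 10-year comparison with an untreated benchmark as added after enrolment closed (recruitment ended in October 2014 according to the synopsis). Do not base it on a fixed event count out of 120. Compare observed events with those expected from the woman-years at risk before oophorectomy or end of follow-up, using untreated rates matched to mutation status and age. Note that women with STIC or invasive cancer on the specimen are excluded from the analysis set (section 8-8-2), which an untreated benchmark may not mirror.

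Items 1 to 3 need wording and one reported limit, with no new patients or data. Item 4 applies only if such a comparison is wanted, and it needs matched external rates that the protocol does not supply. The real cost is that the 3-year result can no longer be presented as positive evidence of protection.

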| Duration of recruitment:              | 33 months (OCT2014)                                                                                                                                                                                                                                                                                                                                                                                                                                                                                                                                                                                                                                                                                                                                                                                                                                                                                                                                                                                                                                                                                                                                                                                                                                                                                                                                                                                                                                                                                                                                                                                                                                                                                                                                                                                                                                                                                                                                                                                                                                                                                                                                                                        |                     |         |                          |                     |               |                     |

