### **8-7 Endpoints**

#### **8-7-1 Pelvic cancer**

The cumulative incidence of pelvic cancer will be estimated by measuring the time-to-onset of pelvic cancer, defined as time from the date of the fimbriectomy to the date of the ovarian cancer, high-grade primary peritoneal cancer, or cancer of other gynecologic pelvic location, with death without pelvic cancer considered a competitive event. Study withdrawal for oophorectomy is also a competitive event. Patients alive without pelvic cancer or oophorectomy based on most recent information are censored at this time.

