#### **8-8-2 Statistical analysis**

The statistical analyses will be performed by the Oscar Lambret Center Methodology and Biostatistics Unit (*Unité de Méthodologie et de Biostatistique*, UMB).

The study populations will be as follows:

- The descriptive analysis of baseline characteristics will be performed on the patient population enrolled in the study.
- The descriptive analysis of the procedure, disease, morbidity, and satisfaction questionnaire will be performed on the patient population who underwent radical fimbriectomy.

- The analysis of cumulative incidence of pelvic cancer, breast cancer, and secondary oophorectomy will be performed on the patient population who underwent surgery and excluding patients with invasive cancer or STIC on the fimbriectomy specimen.
- The analysis of secondary oophorectomy complications will be performed on the patient population who underwent oophorectomy secondary to the fimbriectomy.

The statistical analysis of baseline characteristics, procedure, and disease will be essentially descriptive in nature and will be presented in summary tables including the number of missing data. Continuous variables will be summarized by median and extreme values, and mean and standard deviation if warranted. Categorical variables will be presented as contingency tables (absolute frequency and percentage of each modality).

The inclusion and exclusion criteria will be verified from the data recorded in the case report forms. Any protocol deviations will be detailed, as well as the causes of ineligibility and non-evaluability.

The cumulative incidences of pelvic cancer, breast cancer, and secondary oophorectomy will be estimated by the competitive risk method (Kalbfleish [*sic*: Kalbfleisch] and Prentice), as defined in section 8.7 (endpoints).

In secondary analysis, cumulative incidences of pelvic cancer and breast cancer will be estimated based on age reached.

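### The final rule counts pelvic tumours at a calendar date, with no 36-month limit per woman, but judges them against a 3-year rate of 3%

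*Protocol*

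**What the plan says.** Section 8-8-1 of the protocol, repeated in the synopsis, starts from a natural-history figure: "The cumulative incidence of pelvic tumors is estimated to be around 10% at 10 years in BRCA mutated women". It takes this as "corresponding to an “acceptable” rate of 3% at 3 years".

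Two decision rules follow in the same paragraph:

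- **Interim:** "discontinue the study if, within 3 years, the number of pelvic tumors reaches 2 for 12 participants", with further boundaries of 3 in 27, 4 in 46 and 5 in 66. This rule carries a 3-year limit.
- **Final:** "Three years after the last patient is enrolled, if 8 pelvic tumors are observed among the 120 patients", the strategy is judged insufficiently promising, because the one-sided 90% lower limit then lies above 3%. The only time reference is the calendar date of the count.

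The synopsis gives recruitment as January 2012 to October 2014, 33 months. Section 8-7-1 defines the primary endpoint as time from fimbriectomy to pelvic cancer, with death and oophorectomy as competing events: "Patients alive without pelvic cancer or oophorectomy based on most recent information are censored at this time". Section 8-8-2 estimates the cumulative incidence by the Kalbfleisch-Prentice method in operated women, "excluding patients with invasive cancer or STIC on the fimbriectomy specimen". Section 8-5 ends follow-up at menopause and lists oophorectomy, patient decision, loss to follow-up and death as reasons for withdrawal.

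**The concern.** The 3% is tied to 36 months of exposure. The final count is tied to a date on which only the last woman enrolled has reached about 36 months and the first could have reached 69. Nothing in the protocol limits the final count to 36 months per woman, and nothing raises the 3% to match longer exposure.

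At stake is the rule that decides whether the strategy is abandoned. Taken literally, its false-alarm rate depends on how fast women were recruited and how long they stayed. A strategy with a true 3-year rate of exactly 3% could fail because of tumours that arose in year 4 or 5.

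**Working it through.** **Inputs.** From 8-8-1: reference 3% at 36 months; final boundary 8 of 120; one-sided 90% interval. From the synopsis: accrual of 33 months. Assumed, because the protocol does not give them: constant hazard, uniform accrual, and the exit rates in step 4. Interim looks are ignored, so these are single-look probabilities.

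**1. The plan's own figure.** 8/120 = 6.7%. The exact (Clopper-Pearson) one-sided 90% lower limit is 3.9%, so the statement that it excludes 3% reproduces. For one woman at 3% risk, the binomial tail is P(X ≥ 8 | n = 120, p = 0.03) = 2.9%.

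The interim pairs are also plain binomial comparisons with 3%. P(X ≥ r | n, 0.03) is 4.9% for 2/12, 4.6% for 3/27, 4.9% for 4/46 and 4.8% for 5/66. These boundaries presuppose a risk of 3% for every woman, that is, 36 months each.

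**2. Exposure at the final date.** Last woman: 36 months. First woman: 36 + 33 = 69 months. Mean under uniform accrual: (36 + 69)/2 = 52.5 months. This is potential follow-up.

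**3. Literal count, no exits.**

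- Hazard: λ = −ln(0.97)/36 = 0.000846 per month.
- Mean risk over follow-up uniform on 36 to 69 months: 1 − [exp(−36λ) − exp(−69λ)]/(33λ) = 1 − (0.9700 − 0.9433)/0.02792 ≈ 4.34%.
- Expected tumours: 120 × 0.0434 = 5.2, against 120 × 0.03 = 3.6 with a 36-month window. The share after month 36 is 1 − 3.0/4.34, about 31%.
- P(X ≥ 8 | n = 120, p = 0.0434) = 15.2%, against 2.9%.

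Sensitivity to the accrual pattern: with linearly early-weighted enrolment it is 21.8%, with late-weighted enrolment 9.8%.

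**4. Literal count with competing exit.** With exit hazard h, the risk by time t is λ/(λ+h) × [1 − exp(−(λ+h)t)], averaged over 36 to 69 months. λ is held at the value in step 3.

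| Exit per year | Mean risk, all follow-up | P(≥ 8 of 120), literal | Risk at 36 months | P(≥ 8 of 120), 36-month window |
|---|---|---|---|---|
| 0 | 4.34% | 15.2% | 3.00% | 2.9% |
| 5% | 3.89% | 9.7% | 2.79% | 2.0% |
| 10% | 3.50% | 6.1% | 2.59% | 1.3% |
| 15% | 3.17% | 3.8% | 2.42% | 0.9% |

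The nominal 10% is exceeded with no exits and just met at 5% per year. In every row the literal count is roughly four to five times as likely to reach the boundary as the windowed count.

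**The case against.** The best defence is that the final rule was meant to carry the same window. The paragraph moves from a 3-year rate to a 3-year interim limit to a date three years after the last enrolment. That date is the earliest at which every woman could have completed 3 years, so it can be read as the time when the 3-year count becomes complete. The interim boundaries fit that intention. This is plausible, and it is why the point is a should-fix. It does not remove the point: the final sentence does not repeat the limit, and its own time phrase is a calendar cut-off.

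Exits also matter. Women leave at oophorectomy or menopause, and section 6-2 expects later castration. With exits of 5% per year or more, the literal rule stays below 10%. That stands, and it limits the size of the problem.

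Two stronger readings are tempting and not supported:

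- A reader might infer that the count wrongly keeps oophorectomised women in the denominator, so that the rule does not test the endpoint at all. Section 8-7-1 makes oophorectomy and death competing events, and a competing-risks cumulative incidence keeps those women in the denominator too. Without censoring before month 36, a 36-month count divided by n equals the 36-month cumulative incidence. Only loss to follow-up, patient decision and end of follow-up at menopause separate the two.
- A reader might infer that excluding women with occult lesions lowers the threshold from 8 to 7. That argument needs a one-sided 95% level, which the protocol does not state. At the stated 90% level, 7 of 120 already has an exact lower limit of 3.3%, so the smaller denominator is not what moves it. The fit between the stated level and the boundary of 8 is a separate matter. The synopsis also records that 3 women were added to replace some who could not be assessed, such as non-operated patients.

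**Conclusion.** The point holds as a defect of wording with a measurable consequence. As written, the final rule compares a count over 36 to 69 months of potential follow-up with a 3-year rate. At a true 3-year rate of 3%, under constant hazard and uniform accrual, the chance of wrongly calling the strategy insufficiently promising is 15.2% with no exits and 9.7%, 6.1% or 3.8% with exits of 5, 10 or 15% per year. With a 36-month window the figures are 2.9%, 2.0%, 1.3% and 0.9%. The protocol gives no exit rates, so the actual value within this range is unknown.

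The error runs towards rejecting the strategy, not towards a false success. The cumulative incidence analysis in 8-8-2 is not affected. Severity: should-fix.

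**What to change.** In 8-8-1 and the synopsis, state that the final decision counts only tumours diagnosed within 36 months of each woman's fimbriectomy, in the population defined in 8-8-2, and state the number of women to which the threshold applies. Alternatively, to handle women censored before month 36, base the decision on the Kalbfleisch-Prentice cumulative incidence at 36 months and compare its one-sided lower confidence limit with 3%.

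Later tumours stay in the cumulative incidence curve and are reported there. The cost is a change of wording in two places, with no new data or patients. The downside is that tumours after month 36 no longer enter the decision. Because the current text already reports final enrolment, the change should be recorded as a dated clarification, made without reference to the tumour count.

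### The stated one-sided 90% criterion is already met at 7/120, not first at 8/120, and the printed stopping rules carry an undisclosed false-stop probability of about 12% at a true 3% rate

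*Protocol*

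**What the plan says.** Protocol section 8-8-1, repeated in section 5 (synopsis, methodology and number of patients), takes as its reference an acceptable "rate of 3% at 3 years", derived from a figure of about 10% at 10 years without prophylactic surgery. It then sets two rules.

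- **Interim.** Over a 3-year horizon, the trigger for discontinuation is that "the number of pelvic tumors reaches 2 for 12 participants, 3 for 27 participants, 4 for 46 participants, and 5 for 66 participants". At most 120 patients are planned. These limits are said to compare the "lower limit of the confidence intervals adjusted on the information fraction and on a concave alpha spending function". Neither the function, nor the total alpha, nor the type of interval is given.
- **Final.** Three years after the last enrolment, "if 8 pelvic tumors are observed among the 120 patients", the strategy is judged insufficiently promising because the "lower limit of the one sided 90% confidence interval will not contain the acceptable value of 3" (per cent).

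The 90% in the final rule is the only confidence level in the section. No overall error probability is stated. The synopsis adds that enrolment has ended, with recruitment running to October 2014.

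**The concern.** The final rule gives a count and a reason for the count. If the reason already holds at a smaller count, there are two rules, and they disagree for at least one possible result. This is the trial's only success-or-failure criterion, so the disagreement decides how the result is read.

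The interim rule is described as adjusted for repeated looks, but the reader is given no figure for the error that results. The limits can be checked directly against the reference rate of 3%. If the attained error is above what the one stated confidence level suggests, a report that cites the adjustment would give a better impression of error control than the rules deliver.

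**Working it through.** **Inputs, all from section 8-8-1.** Reference rate p0 = 3% at 3 years; interim limits 2/12, 3/27, 4/46 and 5/66; maximum 120; final cut-off 8/120; one-sided 90% lower limit. Each participant is treated as a complete yes/no outcome at 3 years, as the protocol's own rule does.

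**Step 1: the final rule.** The exact (Clopper-Pearson) one-sided lower limit at level 1 − a exceeds 3% exactly when P(X ≥ k | n = 120, p = 0.03) is below a.

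| Tumors in 120 | P(X ≥ k) at 3% | One-sided 90% lower limit | One-sided 95% lower limit |
|---|---|---|---|
| 6 | 0.153 | 2.65% | below 3% (tail above 0.05) |
| 7 | 0.0703 | 3.27% | 2.77% |
| 8 | 0.0286 | 3.92% | 3.36% |

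The protocol's sentence about 8/120 is reproduced: 3.92% is above 3%. But 7/120 satisfies the same sentence, since 0.0703 is below 0.10. This does not depend on the interval chosen: at 7/120 the one-sided 90% lower limit is 3.09% by Wald, 3.59% by Jeffreys and 3.64% by Wilson. The count of 8 is the smallest that excludes 3% at one-sided 95%, the lower end of a two-sided 90% interval.

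A count of 7 is a realistic outcome. Ignoring the interim looks, P(exactly 7 of 120) is 4% at a true rate of 3% and 15% at 6%.

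**Step 2: the interim limits.** For the first, P(X ≥ 2 | 12, 0.03) = 1 − 0.97^12 − 12 × 0.03 × 0.97^11 = 1 − 0.6938 − 0.2575 = 0.0486 (unrounded). In the same way:

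| Limit | Tail at the printed n | Tail at n + 1 |
|---|---|---|
| 2/12 | 0.0486 | 0.0564 |
| 3/27 | 0.0462 | 0.0506 |
| 4/46 | 0.0488 | 0.0521 |
| 5/66 | 0.0481 | 0.0508 |

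Each printed n is the largest at which a single-look exact test of 3% has a tail of at most 5%. The same sequence would continue at 6/88 and 7/110, and it gives 8 at 120.

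**Step 3: the cumulative false-stop probability.** An exact recursion follows the tumor count participant by participant at p = 0.03. At each look it removes the probability that has reached the limit and adds it to the total.

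| After look at n = | Added | Cumulative |
|---|---|---|
| 12 | 4.86% | 4.9% |
| 27 | 2.53% | 7.4% |
| 46 | 2.09% | 9.5% |
| 66 | 1.54% | 11.0% |
| 120 (cut-off 8) | 0.98% | 12.0% |

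With 6/88 and 7/110 added, the total is 13.6%. With the present interim limits and a final cut-off of 7, it is 14.3%.

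**The case against.** Four points can be made for the protocol.

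1. **The sentence about 8/120 is literally true.** Its lower limit is 3.92%, and the protocol does not say that 8 is the smallest such count. This stands. The slip may lie in the label (one-sided 95% or two-sided 90% intended) rather than in the number. It does not remove the conflict at 7.

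2. **The match to flat 5% tests does not show that no adjustment was made.** A reader might infer from Step 2 that the claimed alpha spending does not exist. The protocol does not support that, because it names neither the interval nor the function, and other constructions give the same numbers. A Wilson lower limit at one-sided level 0.02(2t − t²), with t = n/120, yields 12, 27, 46 and 66. So does a logit lower limit at 0.025·t^0.45. Both make 8 cross at 120 and 7 not cross. Neither is claimed to be the sponsor's formula. Step 3 is unaffected, because it uses only the printed limits.

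3. **No overall 10% error is promised.** The 90% is attached to the final interval only. So 12.0% exceeds what that level suggests, but it does not breach a stated limit.

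4. **The silence between 66 and 120 is not an absence of oversight.** A reader might infer that an excess in that range would go without action. Section 10.6 provides an independent committee that can meet if pelvic cancer incidence is high. What is missing is a numerical limit, not a route to action.

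**Conclusion.** The final rule is inconsistent as written: a count of 7/120 passes by the number and fails by the stated reason, by every interval method tried. The printed rules together carry an exact false-stop probability of 12.0% at a true 3%, of which 11.0% is reached by the fourth look. The protocol discloses no overall error.

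The documents do not show that the cut-off of 8 is itself wrong, that the interim limits were never adjusted, or that a stated 10% overall error is broken. The first could equally be a mislabelled level, the second cannot be settled without the function used, and the third figure is not in the protocol.

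The figures assume a true 3-year rate of exactly 3%, complete 3-year outcomes at the listed numbers of participants, and looks only at those numbers. If the same rule was also applied at 6/88 and 7/110, the total is 13.6%.

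**What to change.** In section 8-8-1 and the synopsis:

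- Keep 8/120 and describe it as the count at which the exact one-sided 95% (two-sided 90%) lower limit exceeds 3%, with the values 2.77% at 7 and 3.36% at 8. A count of 7 then has one verdict.
- If one-sided 90% is really meant, the cut-off is 7/120, and the overall error to state is 14.3%. Lowering the cut-off therefore does not improve error control.
- Leave the four interim limits unchanged, because accrual is complete and rewriting them now would be retroactive.
- Name the interval type, spending function and total alpha actually used, or drop the claim of adjustment.
- State the attained overall false-stop probability at 3%: about 12%, or 13.6% if 6/88 and 7/110 were also applied.

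This costs a few lines in two places and needs no new data. The downside is a less favourable stated error rate.
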